# Facilitating return to work through early specialist health-based interventions (FRESH): protocol for a feasibility randomised controlled trial

**DOI:** 10.1186/s40814-015-0017-z

**Published:** 2015-06-17

**Keywords:** Occupational therapy, Return to work, Traumatic brain injury, Vocational rehabilitation, Feasibility, Randomised controlled trial

## Abstract

**Background:**

Over one million people sustain traumatic brain injury each year in the UK and more than 10 % of these are moderate or severe injuries, resulting in cognitive and psychological problems that affect the ability to work. Returning to work is a primary rehabilitation goal but fewer than half of traumatic brain injury survivors achieve this. Work is a recognised health service outcome, yet UK service provision varies widely and there is little robust evidence to inform rehabilitation practice. A single-centre cohort comparison suggested better work outcomes may be achieved through early occupational therapy targeted at job retention. This study aims to determine whether this intervention can be delivered in three new trauma centres and to conduct a feasibility, randomised controlled trial to determine whether its effects and cost effectiveness can be measured to inform a definitive trial.

**Methods/design:**

Mixed methods study, including feasibility randomised controlled trial, embedded qualitative studies and feasibility economic evaluation will recruit 102 people with traumatic brain injury and their nominated carers from three English UK National Health Service (NHS) trauma centres. Participants will be randomised to receive either usual NHS rehabilitation or usual rehabilitation plus early specialist traumatic brain injury vocational rehabilitation delivered by an occupational therapist. The primary objective is to assess the feasibility of conducting a definitive trial; secondary objectives include measurement of protocol integrity (inclusion/exclusion criteria, intervention adherence, reasons for non-adherence) recruitment rate, the proportion of eligible patients recruited, reasons for non-recruitment, spectrum of TBI severity, proportion of and reasons for loss to follow-up, completeness of data collection, gains in face-to-face *V*s postal data collection and the most appropriate methods of measuring primary outcomes (return to work, retention) to determine the sample size for a larger trial.

**Discussion:**

To our knowledge, this is the first feasibility randomised controlled trial of a vocational rehabilitation health intervention specific to traumatic brain injury. The results will inform the design of a definitive trial.

**Trial registration:**

The trial is registered ISRCTN Number 38581822.

**Electronic supplementary material:**

The online version of this article (doi:10.1186/s40814-015-0017-z) contains supplementary material, which is available to authorized users.

## Background

Approximately 1.4 million people in the UK sustain traumatic brain injury (TBI) each year [1] and up to 150,000 incur moderate or severe injury [2] resulting in cognitive and psychological problems that interfere with daily living activities including work. The societal cost of TBI in terms of diagnostic tests, treatment, rehabilitation, lost time at work and dependency on benefits is estimated at 2.8 billion Euros per year in Germany (price year unclear but survey conducted 2000/1) [3]. It is also a known cause of personal bankruptcy [4]. People who do not return to work are more likely to be depressed [5].

Returning to work is a primary rehabilitation goal yet reported success varies widely. Only around 41 % of TBI survivors who were working before their injury are in work at 1 and 2 years later [6]. The reasons for this are complex. Systematic reviews of factors predicting a return to work following TBI are inconclusive [7–10]. Biomedical factors such as injury severity or post injury physical or neuropsychological function alone do not fully explain work outcomes. Personal, environmental, social and organisational factors are also known to influence outcome success in supporting people with long-term conditions to return to work [11]. Whilst study heterogeneity and known difficulty in following people with TBI up over time [12] explain some of the difference in reported TBI work outcomes, inadequate rehabilitation cannot be excluded as a cause. Keeping people with TBI in work is also problematic. Many TBI survivors return prematurely but leave once the impact of the brain injury on their job is realized [13].

### What is vocational rehabilitation?

Vocational rehabilitation (VR) is defined as “whatever helps someone with a health problem to stay at, return to and remain in work” [14]. It involves helping people find work, helping those who are working but having difficulty and supporting career progression in spite of illness or disability. It is recognised as an important outcome of the UK National Health Service (NHS) health interventions [15], as a role for healthcare professionals [16] and recommended in clinical guidelines for TBI [17–19]. However, health services supporting people with TBI in returning to work are rare in the UK [20, 21]. For many people with TBI, NHS provision does not typically extend to VR. When it does, this is often towards the end of rehabilitation, after goals for independence in mobility and daily function have been achieved. People with milder head injuries and/or hidden disabilities, such as cognitive, hearing or visual impairment and those with milder TBI, are often discharged without follow-up.

There is a lack of evidence to support the effectiveness or cost effectiveness of VR for people with TBI. Whilst rehabilitation interventions for people with TBI have been evaluated using randomised controlled trials and work outcomes reported [22, 23], these were military trials and the interventions not specific to vocational rehabilitation. In a systematic review of vocational rehabilitation models, Fadyl et al. [24] identified only one randomised controlled trial (*n* = 22) that included a mixed acquired brain injury sample and only seven people with a traumatic brain injury [25].

In a single-centre cohort comparison, an early TBI specialist vocational rehabilitation intervention (ESTVR) delivered by an occupational therapist (OT), supported by a TBI case manager was compared to usual NHS rehabilitation (whatever support was available locally) and found it to be more effective (27 % more people with moderate and severe TBI in work at 12 months) at returning people with TBI to work and keeping them there 12 months after injury than usual care [26]. The mean per-patient difference in health and social care costs was only £75.00. This was because usual care participants received roughly the same amount of input but from GPs and other non-coordinated community services.

The primary focus of the ESTVR intervention was on preventing job loss by identifying people early after injury and focusing on timely returning to work with an existing employer (job retention). However, as ESTVR was an existing part of traumatic brain injury service provision in Nottingham and the intervention was delivered by a single therapist in one centre, uncertainty exists as to whether the successful outcomes were attributable to ESTVR and whether it can be delivered by therapists elsewhere.

### Aim

The primary aims are to assess the feasibility of (i) delivering early specialist traumatic brain injury vocational rehabilitation (ESTVR) in three NHS regional TBI referral centres in a way that is acceptable to people with TBI, NHS staff and employers when compared to usual NHS rehabilitation and of (ii) conducting a randomised controlled trial comparing ESTVR in addition to the usual NHS rehabilitation with usual NHS rehabilitation alone. In addition, we aim to identify the primary outcome of importance of ESTVR to service providers, service users and employers. This will enable us to determine whether a definitive evaluation trial is feasible and, if so, how its design can be optimised.

### Study objectives

In addition, we will:assess the integrity of the study protocol (e.g. inclusion/exclusion criteria, staff training, adherence to intervention, and identify reasons for non-adherence);estimate the recruitment rate and the proportion of potentially eligible TBI patients recruited and identify reasons non-recruitment (missed, medical, logistic, others);estimate the proportion of participants lost to follow-up and the reasons for loss to follow-up;determine the spectrum of TBI severity among recruits;explore the views of TBI patients and staff on recruitment and the acceptability of randomisation;determine the most appropriate method(s) of measuring key outcomes (return to work, retention);estimate parameters necessary to calculate sample size for a larger trial (e.g. rate of return to work at 12 months in control group);explore the completeness of data collection for potential primary outcome(s) for a definitive trial;explore potential gains in using face-to-face rather than postal data collection; andinvestigate how return to work is related to mood, wellbeing, function, work capacity, social participation, quality of life and carer-strain.

In a series of embedded qualitative studies, we will explore retrospectively the following items:What service interventions are most valued in practice by an employee with TBI?What service interventions are most valued in practice by an employer?Clinical NHS staff views of the acceptability and usefulness of the ESTVR training package, including the manual and mentoring system.Service user, employer and NHS staff views on factors likely to affect the ESTVR implementation and clinical delivery in the NHS.

## Methods/design

Mixed methods: Feasibility individually randomised parallel-group controlled trial with embedded qualitative evaluation and feasibility economic evaluation can be seen in Fig. 1.

**Fig. 1 Fig1:**
[figure not shown]
Mixed methods study configuration: interaction between feasibility trial, feasibility economic evaluation and qualitative and quantitative sub studies

### Participants

Adults (aged 16 and above) living in the London, Preston and Leeds health communities and admitted for 48 h or more with new TBI and who were either in work (paid or unpaid) or in full-time education prior to their injury. Those not intending to return to work/study, unable to consent for themselves or living more than 1 h (or reasonable) travelling distance from the recruiting centre will be excluded. Nominated carers of recruited patients will also be invited to take part. Carers who are not nominated by a TBI participant will be excluded. We will attempt to include people with a language barrier or in whom English is not their first language.

### Identification and recruitment of trial participants

Potential participants will be identified by members of the existing clinical care team using existing TBI registers. The initial approach will be from a member of the patient’s usual care team, who will provide information sheets and notify the research team. The research team (research assistant or research network nurse) will inform potential participants of all aspects pertaining to participation in the study.

The University of Nottingham’s (sponsor) screening log will be used to monitor and identify recruitment against eligibility criteria and demonstrate that recruits are representative of the group as a whole. The proportion of refusals and reasons for refusal (where given) will be recorded. Every person with TBI admitted fitting the inclusion criteria during the trial recruitment period will be entered onto the screening log by the research assistant or research network nurse. Minimum data recorded will be age, gender, meeting eligibility criteria (Y/N), consented (date) or reason for non-consent.

Discharged patients will be sent a participant information sheet with covering letter from the consultant informing them about the project and stating that the researcher will contact them to ask if they are interested in taking part. If the patient expresses interest, then an appointment will be made for the researcher to visit, answer any questions and, if applicable, take informed written consent.

Consenting TBI participants will be asked to nominate a carer (spouse, partner, parent or person with whom they have most contact) during the baseline assessment visit. Carers will be sent a carer’s information sheet and covering letter from the consultant informing them about the project and stating that the researcher will contact them to ascertain their interest in taking part. Interested carers will be visited by a member of the research team to take written consent. Carers will only be recruited with consent from the TBI participant.

Completeness of carer recruitment will be verified by crosschecking TBI participants with nominated carers and the proportion of identified consenting carers recruited. This will be done by the research assistant employed in each centre.

The process for obtaining participant informed consent will be in accordance with Research Ethics Committee guidance and Good Clinical Practice. The investigator or their nominee and the participant shall both sign and date the informed consent form before the person can participate.

Baseline assessments will be completed prior to randomisation and within 8 weeks of TBI (this time frame was based on data from the original cohort comparison study where most recruitment occurred within 5 weeks of injury and because we were keen to ensure that participants received early intervention to prevent job loss). All baseline measures will be collected face-to-face by the research assistant or research nurse either in hospital or at the participant’s home if they have been discharged at the time of recruitment.

### Randomisation

Patient participants will be randomised by the research assistant using stratified randomisation (strata based on centre) via a computer-generated random allocation sequence created by Nottingham Clinical Trials Unit accessed via the web. The randomisation will be based on a computer-generated pseudo-random code using random permuted blocks of randomly varying size, created by Nottingham CTU in accordance with their standard operating procedure and held on a secure server.

The participants will be un-blinded to the intervention group allocation. Other members of the research team (chief investigator, health economist, data coordinator and trial management team) including the research assistant responsible for collecting face-to-face follow-up outcome measures and data entry staff will be blinded to group allocation. Allocation will remain concealed until all interventions are assigned and recruitment, data collection, and analyses complete.

Each participant will be assigned a trial identity code, allocated at randomisation, which will be used on case report forms, other trial documents and the electronic database. The documents and database will also use their initials and date of birth.

### Intervention and comparator

#### Early specialist traumatic brain injury vocational rehabilitation (ESTVR)

Participants (TBI patients) randomised to the intervention group will receive all usual NHS rehabilitation interventions but, in addition, will receive ESTVR (as required) targeted at job retention.

ESTVR is an early, TBI specialist, vocational rehabilitation job retention model. It was developed in Nottingham by an occupational therapist and is routinely delivered as part of usual NHS rehabilitation by the Nottingham Traumatic Brain Injury Service. It was evaluated in a single-centre cohort comparison study [27], and the results suggested a positive influence on 12-month work outcomes in those who received it. ESTVR is a case coordination model [24] based on best practice guidelines for vocational rehabilitation following acquired brain injury [19]. It is delivered by an occupational therapist, supported by a health-based case manager both of whom have knowledge and skills in working with people with a TBI and in vocational rehabilitation. Most interventions are delivered in the community.

People with TBI are identified early (at point of injury) and the intervention aims to prevent job loss. The vocational rehabilitation intervention seeks to lessen the impact of TBI by assessing the patient’s role as a worker and finding acceptable strategies to overcome problems, e.g. assessing and addressing new disabilities which might impact directly on work activities. The intervention process follows three stages, assessment, intervention, monitoring and review. Detailed assessment of the person’s occupational status and vocational aspirations and functional capacity for work, is followed by intervention to prepare the TBI person for work by providing pre-work training and establishing structured routines with gradually increasing activity levels; opportunity to practice work skills, e.g. computer use to increase concentration, cooking to practice multi-tasking. The occupational therapist liaises with employers/tutors and employment services to advise about the effects of TBI and plan and monitor-graded work return, conduct worksite visits and job evaluations, identifies the need for workplace or job adaptations and serves as the link between health and employment services to access additional support. During *monitoring and review*, progress is reviewed and ongoing advice, support and feedback provided for TBI patient, family and employer (supervisor and work colleagues as appropriate) with ongoing liaison with employment services if needed. TBI case managers coordinate the overall TBI care package and provide support, education and advice to patients, family and others, e.g. NHS staff, social services, headway and solicitors, remaining in contact with patients and families whilst there are achievable rehabilitation goals.

The intervention is tailored to individual needs according to the following menu of components:assessing people’s functional capacity for work;detailed job evaluation and safety assessment;liaison with employers regarding necessary accommodations (equipment and adaptations) and graduated return to work programmes;individual work-related goal setting and problem-solving sessions;partnership working with statutory and voluntary service providers such as disability employment and benefits advisors and headway;negotiating voluntary work placements, andproviding information and advice to TBI patients, their families and employers and counselling.

A manualised training programme, developed in advance of the trial and based on the original Nottingham Pilot [26, 27], will be delivered centrally to occupational therapists and case managers (a nominated member of the rehabilitation team who will be trained to adopt a vocational rehabilitation case manager role) in each of the three NHS centres. The training and intervention delivery will be supported by telephone and email mentoring. Intervention delivery will be quality monitored and fidelity checks implemented to assess adherence to the ESTVR model.

#### Control: usual NHS rehabilitation

Participants allocated to the control group will avail themselves of usual health and social care services as necessary.

We will attempt to measure and describe the current focus of usual care by including resource use questions in our outcome measurement. In addition, efforts to support people with TBI in a return to work in usual NHS rehabilitation (UC) will be gathered in qualitative interviews with usual care participants.

#### Concomitant therapy

There are no known issues with the intervention and concomitant treatments, therefore no concomitant treatments will be excluded. Information on participants’ use of other community rehabilitation, social care and third-sector services will be recorded as part of the assessment of feasibility.

### Follow-up

Follow-up assessments will be completed by a research assistant masked to treatment allocation in one centre and by postal questionnaire in two centres. Steps will be taken to minimise missing data by personal contact and text messaging to prompt returns. Every attempt will be made to locate participants for follow-up.

The trial manager, or where required, a nominated designee of the sponsor (University of Nottingham), shall carry out monitoring of trial data as an ongoing activity. Entries on case report forms will be verified by inspection against the source data. A sample of case report forms (10 %) will be checked for verification of entries. In addition, the subsequent capture of data on the trial database will be checked. Where corrections are required, these will carry a full audit trail and justification.

Outcome data will be entered by a data manager blind to treatment allocation at Lancashire Clinical Trials Unit. Electronic data will be backed up every 24 h to both local and remote media in encrypted format.

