As the likely primary measure of effectiveness for the main trial is work status at 12 months defined as competitive employment (full- or part-time paid work in an ordinary work setting, paid at the market rate) [29], we will record as the success criteria for the intervention at 12 months post randomization, the proportion of persons returned to and retained in:work in the same role with an existing employer;work in a different role with an existing employer;work with a different employer, i.e. new work, same or a different role; andself-employed work.

This will be collected by postal questionnaire using a series of bespoke work focussed questions.

Secondary measures of effectiveness collected at 3-, 6- and 12-month post randomisation include hospital anxiety and depression scale [30], extended activities of daily living [31], community integration questionnaire [32], EuroQol EQ-5D-3 L [33], work productivity and activity impairment questionnaire [34], carer-strain index [35], self-efficacy question from the work ability index [36] and data on the use of health and social care resources, including GP, nurse, therapists, employment services and medication use. At 12 months, the Glasgow outcome scale score will be collected as a measure of TBI recovery. This will help determine the sensitivity of measures/their value and any change related to the ESTVR intervention.

The schedule of assessments is shown in Table 1

**Table 1 Tab1:** Schedule of assessments for patients and carers

Measure		Follow-up time points		
	Baseline	3 months	6 months	12 months
Schedule of assessments (patients)				
Demographic information	☑	-	-	-
Duration PTA	☑	-	-	-
GCS score	☑	-	-	-
Duration unconsciousness	☑	-	-	-
Specific VR-focused questions	☑	☑	☑	☑
EQ-5D-3 L (Euro-QOL)	☑	☑	☑	☑
Hospital anxiety and depression scale (HADS)	☑	☑	☑	☑
Nottingham extended activities of daily living (NEADL)	☑	☑	☑	☑
Community integration questionnaire (CIQ)	☑	☑	☑	☑
Resource use of health and social care	☑	☑	☑	☑
Self-efficacy—single question from work ability index	☑	☑	☑	☑
Work productivity and activity impairment questionnaire V2 (WPAI)	☑	☑	☑	☑
Glasgow outcome scale score (GOS)				☑
Schedule of assessments (carers)				
Carer strain index (CSI)	☑	☑	☑	☑
Specific impact on carer’s work questions	☑	☑	☑	☑

The proposed flow of participants through the study is shown in Fig. 2.

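### Follow-up mode is fixed by centre, so the face-to-face versus postal objective can give only a between-centre description; the collection mode for 12-month work status is also stated inconsistently

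*Protocol article*

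**What the plan says.** All from the protocol article.

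- **Follow-up:** "Follow-up assessments will be completed by a research assistant masked to treatment allocation in one centre and by postal questionnaire in two centres".
- **Study objectives:** one of the additional objectives is to "explore potential gains in using face-to-face rather than postal data collection". The abstract's Methods/design paragraph words this more strongly. Among the secondary quantities to be measured it lists "completeness of data collection, gains in face-to-face" over postal collection.
- **Randomisation:** treatment is the only thing randomised, with centre as the stratification factor. The research assistant carries out the randomisation. The blinded staff are listed as "including the research assistant responsible for collecting face-to-face follow-up outcome measures and data entry staff will be blinded to group allocation", which confirms that some follow-up outcomes are collected in person.
- **Identification and recruitment of trial participants:** "All baseline measures will be collected face-to-face by the research assistant or research nurse", so baseline gives no contrast between modes.
- **Assessment of objectives:** of work status at 12 months, the likely primary measure for the main trial, it says "This will be collected by postal questionnaire using a series of bespoke work focussed questions". No centre is excepted. Table 1 lists the work-focused questions at baseline and at 3, 6 and 12 months.
- **Analysis:** eligibility, consent and attrition rates are described overall and by site with 95% confidence intervals, and no p values are reported.

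**The concern.** An objective about the gain from in-person follow-up needs people who are alike apart from the mode used. Here one centre supplies the whole face-to-face group and two others supply the whole postal group. Those centres may differ in case mix, staff and local services, and any such difference appears in the data as an apparent mode effect or hides a real one.

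The article's Background notes that people with TBI are hard to follow over time, so how to collect outcomes is a real question for the definitive trial. If the contrast is read as a mode effect, that choice would be informed by a comparison of centres.

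The statement that work status comes by post raises a second problem. Taken literally, the mode comparison would leave out the outcome most likely to be primary. Otherwise, the sentence misdescribes the face-to-face centre. The mode matters for interpreting both the completeness of the primary endpoint and the control-arm work rate, which the article intends to use when planning the next trial.

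**Working it through.** **Inputs.** From the article: 102 participants, three centres, one face-to-face and two postal, attrition assumed to be at most 15% (so completeness of 85% or more). Assumed here: an equal split of 34 per centre, since the split is not stated; 75% completeness as an alternative value for the postal group; and a between-centre SD of 5 or 10 points for reasons unrelated to mode. The documents give no source for that SD.

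**The article's own precision figures (Sample size justification).** The half-width is 1.96 × √(p(1−p)/n).
- Attrition, p = 0.15, n = 100: 7.0 points, as stated.
- Recruitment, n = 300: 5.3 points at p = 1/3 and 5.7 at p = 0.5. The latter rounds to the stated 6.

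These figures concern overall rates and are not in dispute.

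**Can mode be separated from centre?** Call the face-to-face centre A and the postal centres B and C. The face-to-face indicator equals 1 − B − C exactly. An intercept plus indicators for B and C has rank 3. Adding the mode indicator makes four columns, but the rank stays at 3. A mode effect adjusted for centre therefore cannot be estimated at any sample size.

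**Unadjusted contrast, 34 versus 68.**
- 85% in both groups: 1.96 × √(0.1275/34 + 0.1275/68) = 1.96 × √0.005625 = 14.7 points.
- 85% versus 75%: 1.96 × √(0.1275/34 + 0.1875/68) = 15.8 points.

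Both treat centres as interchangeable.

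**Allowing for centre differences (85% in both).** Add SD² × (1 + 1/2), for one centre against the mean of two.
- SD 5 points: 1.96 × √(0.005625 + 0.00375) = 19.0 points.
- SD 10 points: 1.96 × √(0.005625 + 0.015) = 28.1 points.

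The trial cannot properly estimate this SD. Only the two postal centres share a mode, which leaves 1 degree of freedom (t = 12.7).

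**Mode randomised within the face-to-face centre, 17 versus 17.**
- 85% in both groups: 1.96 × √(2 × 0.1275/17) = 24.0 points.
- 85% versus 75%: 1.96 × √(0.1275/17 + 0.1875/17) = 26.7 points.

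**Work status.** The Follow-up and Randomisation sections provide in-person outcome collection in one centre. The section on assessment of objectives gives post as the route for 12-month work status everywhere. For the face-to-face centre these cannot both hold as written.

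**The case against.** The objective is modest. The article says explore, it is one of about ten additional objectives, and no test, threshold or decision rule depends on it. Mode is not on the article's list of what determines feasibility. Description by site with confidence intervals remains possible, and qualitative process data will add to it. All of this stands, and it limits the weight of the point. A reader might infer that the objective cannot be addressed at all. The documents do not support that: what is lost is attribution to mode, not description.

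A reader might also infer that the effectiveness estimate is biased. It is not confounded by mode, because treatment is randomised within centre and both arms in a centre are followed up in the same way.

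The statement about postal collection may be loose shorthand, given the dedicated Follow-up section and the reference to a blinded face-to-face assessor. That is the likelier reading. So the inference that no in-person data on work status will exist is not established, but the text still needs correcting.

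Additional file 1, which sets out how the feasibility objectives are measured, is not shown. It could not remove the confounding unless it changed the allocation of mode.

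Finally, 17 versus 17 is no more precise than the present contrast. That is true. Its advantage is that its error can be stated, whereas the error from centre differences cannot be estimated here.

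**Conclusion.** The concern holds for one exploratory secondary objective. With mode fixed by centre, the trial can describe how completeness differs between one centre and two others, but it cannot say how much of that is due to face-to-face collection. This follows from the allocation itself and needs no numerical assumption. The nominal half-width of 14.7 to 15.8 points rests on the assumed 34 versus 68 split and completeness of 75% to 85%. The range of 19 to 28 points also rests on the assumed between-centre SD and is illustrative only. Recruitment, overall attrition and the treatment comparison are untouched.

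The inconsistency over how 12-month work status is collected in the face-to-face centre is a separate, definite conflict in the text.

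**What to change.** 1. **Preferred.** For participants not yet followed up, randomise follow-up mode within the centre that already has the masked face-to-face assessor. This gives about 17 versus 17 under the equal-split assumption, and fewer if follow-up has begun, since recruitment is already under way. The cost is an amendment, a second allocation and a smaller face-to-face group. The estimate will be imprecise (about 24 points either way at 85% completeness) but not confounded with centre.
2. **If that is not practicable.** Restate the objective in the abstract and Study objectives as a description of completeness by centre, and report that the contrast cannot be attributed to mode. Participants already followed up under the present scheme should be reported this way in any case. This costs only wording.
3. **In either case.** Reconcile the Follow-up section with the statement in the section on assessment of objectives, so that it is clear how work status is collected in the face-to-face centre.
4. **Optional.** Face-to-face visits could be extended to all three centres with mode randomised in each. The article refers to a research assistant employed in each centre, but it also has the research assistant perform randomisation and provides a masked assessor in one centre only. This is workable only if masking can be preserved without extra staff.
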